# A Peer Support Specialist–Delivered Sexual and Intimate Partner Violence Prevention Program for Women in Substance Use Treatment: Protocol for a Single-Arm Trial

**DOI:** 10.2196/68673

**Published:** 2025-08-08

**Keywords:** interpersonal violence, sexual violence, sexual assault, dating violence, partner violence, repeated exposure to violence, intervention, peer recovery coaches, addiction, substance use disorders, drug use

## Abstract

**Background:**

Women in substance use treatment are disproportionately affected by violence. Both a history of violence and substance use place women at risk for cumulative exposure to violence and adverse outcomes, including mental and physical health problems. Interventions are urgently needed to reduce these health disparities by preventing initial and repeated exposure to sexual and intimate partner violence among women with substance use disorders (SUDs). The Healthy Relationships and Interpersonal Violence Education (THRIVE) program adapts evidence-based strategies for this population and is informed by the information, motivation, behavioral skills theoretical model. Topics include the intersection of substance use and violence, consent, risk detection, protective behavioral strategies, and help seeking. THRIVE uses a novel approach by delivering the program via peer support specialists (PSSs), trained advocates in recovery from SUDs who can help overcome barriers to care, including stigma and accessibility.

**Objective:**

The first objective is to determine program acceptability and feasibility. The second objective is to determine the preliminary effectiveness of THRIVE, including its effect on violence-related knowledge and attitudes, protective behaviors, exposure to sexual and intimate partner violence, substance use, and mental health.

**Methods:**

The study entailed a single-arm trial of THRIVE with 71 women in behavioral and medication-assisted substance use treatment, recruited from 3 outpatient and residential treatment sites. Interview data assessing intervention acceptability and feasibility were collected from participants and PSSs. Participants completed assessments at 4 time points over 3 months (baseline, after the intervention, and 1- and 3-month follow-ups). Self-report questionnaires assessed (1) violence prevention knowledge, attitudes, and behaviors; (2) exposure to sexual and intimate partner violence; and (3) substance use and mental health. To determine acceptability and feasibility, both quantitative and qualitative data were collected on feasibility (recruitment and retention), adherence, and acceptability (engagement, perceived usefulness, barriers and facilitators to participation and adoption, and working alliance with PSSs).

**Results:**

Of the 92 women recruited and enrolled, 71 (77%) completed the intervention, 58 (63%) completed the 1-month follow-up, and 44 (48%) completed the 3-month follow-up between June 2024 and March 2025. The mean age of enrolled participants was 35 (SD 9.87) years, and the majority were White (n=79, 86%), followed by Black (n=4, 4%) and other racial and ethnic identities (n=7, 8%).

**Conclusions:**

THRIVE will address critical gaps in the field by (1) expanding violence prevention strategies to SUD treatment settings, (2) integrating sexual and intimate partner violence prevention, (3) incorporating a focus on illicit substance use, and (4) engaging PSSs to overcome barriers to care. The long-term objective of this project is to develop an accessible, scalable, and efficacious prevention program that reduces the incidence of exposure to sexual and intimate partner violence, substance use, and violence-related mental health disorders for women in substance use treatment.

**Trial Registration:**

ClinicalTrials.gov NCT06608979; https://clinicaltrials.gov/study/NCT06608979

**International Registered Report Identifier (IRRID):**

DERR1-10.2196/68673

## Introduction

### Interpersonal Violence History, Substance Use, and Health

A substantial proportion (60%-90%) of individuals in substance use treatment report a history of violence, with women being at greatest risk for initial and repeated exposure to interpersonal violence [1-3]. Interpersonal violence is an overarching term that encompasses both sexual violence (SV) and intimate partner violence (IPV) [4]. SV can be defined as nonconsensual sexual contact through physical force or inability to consent (eg, incapacitation due to drugs or alcohol). It can include harassment, unwanted contact, coerced sex, or attempted or completed rape and more recently has been expanded to include cyber-SV [5,6]. IPV often co-occurs with SV and includes physical violence, SV, stalking, and psychological aggression that occurs in the context of a current or former romantic relationship [7]. Given the high prevalence of interpersonal violence among women with substance use disorders (SUDs), there is an urgent need for interventions to prevent initial and repeated exposure to interpersonal violence in this population.

Interpersonal violence is a critical public health problem associated with a host of physical and mental health outcomes, including posttraumatic stress disorder (PTSD), depression, SUDs, chronic pain, gastrointestinal disorders, and a variety of chronic health conditions [8-10]. In particular, women in SUD treatment with a history of violence are more likely to experience relapse and poor recovery outcomes [11-13]. Both a history of violence and substance use place women at risk for exposure to cumulative interpersonal violence, and two-thirds of women with exposure to SV experience repeated exposure [1,14,15]. Substance use is frequently cited as a coping mechanism for managing posttraumatic stress and the aftereffects of exposure to violence and also places women at risk for exposure to interpersonal violence [1,14]; for example, research has indicated that individuals in treatment for co-occurring disorders such as PTSD and SUD are at greater risk for exposure to violence than individuals with SUD alone [16].

Despite the intersection of trauma and substance use problems, there is a disconnect between trauma-informed services and substance use treatment [17]. Substance use treatment can be defined as behavioral or pharmacological treatment provided by medical and mental health professionals for a range of SUDs (eg, alcohol, opioid, stimulant, polysubstance use) [18]. The Substance Abuse and Mental Health Services Administration (SAMHSA) has proposed a model of trauma-informed care to adopt in behavioral and substance use treatment facilities, further emphasizing the importance of an integrated approach to substance use treatment [19]. Although the acceptance of and evidence for integrated treatments for trauma and SUD have grown, studies indicate that less than half of SUD treatment facilities offer trauma-specific services [17,20,21]. The facilitators of adopting these models include state policies supportive of screening, insurance reimbursement, and evidence-based treatment for trauma [21]. Barriers to implementation include organizational factors such as the logistics of adopting integrated treatments within current service time frames and formats, mental health provider concerns about the timing of trauma treatment initiation or ongoing exposure to violence, lack of mental health provider training, and high case management needs in this population [22]. These studies have primarily focused on the provision of mental health services, and little is known about the promotion of violence prevention programs in SUD treatment settings. Without efficacious violence prevention programs integrated into these settings, women with SUDs will continue to experience trauma-related health disparities.

### Barriers to Care

In addition to a lack of access to integrated service delivery models, women with SUDs and a history of interpersonal violence face multiple barriers to engaging in trauma-informed services and mental health care. Barriers include stigma, lack of acknowledgment of violent incidents, mistrust in formal systems, being a member of a group considered oppressed or minoritized, problematic gender role norms, lack of available resources, and fears of negative consequences [23,24]. Studies indicate that individuals with a history of violence frequently experience multiple co-occurring mental health concerns and, in the face of other barriers to care, are unlikely to seek treatment [25]. Furthermore, individuals with a history of violence and substance use face specific barriers such as lack of acknowledgment of substance-involved sexual assaults as rape, perceived lower credibility by health care providers, and fears of facing criminal charges [23]. These barriers inhibit engagement with prevention and recovery, as well as curtail help-seeking behavior. Furthermore, the strain on health care systems to address the current mental health crisis has limited the availability of mental health professionals to deliver preventive care and clinical interventions [26,27].

### Potential of Peer Support Models to Advance Trauma-Informed Care

The SAMHSA model for trauma-informed care highlights the important role of peer support services in overcoming these barriers and in ensuring a continuum of care. Peer support specialists (PSSs) are individuals who have achieved stable recovery from mental health conditions [28]. Although the definitions of recovery differ between peer-certifying organizations, many align with SAMHSA’s definition, which describes recovery as a process of change to improve health and wellness and strive toward one’s full potential, rather than a symptom-free end state [29]. As such, recovery can be achieved via multiple pathways such as mental health treatment, family and peer support, and faith-based interventions [29]. PSSs use both their lived experience and relevant training to guide and mentor other individuals in treatment or recovery [30]. Peer support programs are based on the principles of mutual respect and support, empowerment, shared responsibility, and an empathy and connection that can be achieved outside of the constraints of a hierarchical (expert and patient) relationship [31]. These programs aim to reduce marginalization and stigma while offering an extension of mental health care beyond the bounds of formal services. PSSs not only offer a means of overcoming resource demands but can also address other significant barriers to care, such as stigma, mistrust in formal systems, and limited availability of mental health providers representing minoritized identities [32]. Peer norms are a significant predictor of substance use as well as both perpetration of and exposure to violence, and the involvement of peers as prevention educators could be especially fruitful in shifting these norms [33,34]. Violence prevention programs are sorely needed in substance use treatment settings, and PSSs can serve as an important resource for offering the tools to prevent initial and repeated exposure to interpersonal violence and the associated mental health sequelae among women with SUDs.

Peer support programs were integrated into formal mental health systems in the 1980s and currently represent one of the fastest growing sectors of the mental health workforce [30]. Research has established the value of PSS models for suicide prevention and the management of mental health conditions [35,36]. In addition, some violence prevention programs have used peers as advocates, with peers being defined as fellow students or adolescents [37,38]. However, studies have yet to evaluate PSS models for offering violence prevention services in various mental health care settings. Our program extends this promising model to implement needed prevention programming via trusted and trained peer facilitators in substance use treatment settings.

### Violence Prevention Programs

Numerous evidence-based programs for SV and IPV prevention have been developed and supported by prior research [39,40]. However, they have almost exclusively been delivered in college and school-based settings, and a recent review has indicated minimal changes in the overall prevalence of SV exposure and perpetration over time [41]. A recent meta-analysis showed that campus SV prevention programs have significant impact on rape myth acceptance, knowledge and attitudes toward sexual assault, knowledge of consent, and exposure to SV [39]. By contrast, a similar meta-analysis highlighted limited behavior change, despite changes in knowledge and attitudes [42]. Most of these programs are geared toward a broad audience of individuals at risk of experiencing SV, potential perpetrators, and bystanders. The enhanced assess, acknowledge, act model is one of the few models to show efficacy for specifically addressing risk for exposure to SV among women by using risk recognition, reducing barriers to active resistance, and engaging in protective strategies [43-45]. Participants demonstrated decreased rape myth acceptance, increased resistance strategies, and decreased incidence of completed rape at 6 months [43]. To our knowledge, very few programs address alcohol or other substance use problems in the context of SV prevention. One web-based program, which used normative feedback on drinking behavior significantly reduced SV risk among women with a history of severe SV and also reduced alcohol use among college women with histories of SV and heavy episodic drinking [46]. Our own team has developed and tested college prevention programs, including a digital app (Make a Change) [47] and a web-based program for college athletes (All In) [48] that used education on consent, protective strategies, and alcohol risk reduction. These programs demonstrated reductions in SV risk factors, including violence-supportive peer norms and drinking behavior [47,48].

Prior programs offer guidance in terms of evidence-based prevention content, although none have been tested among populations seeking treatment or individuals with SUDs outside of alcohol use disorders. Although alcohol use is a commonly cited risk factor for exposure to violence, other substances are associated with IPV and SV; for example, perpetrators use illicit substances to exercise control over their partners through coercing use, encouraging the use of greater amounts, and interfering with recovery. Illicit substance use is also associated with transactional sex, stigma that leads to sexual vulnerability, and financial and relationship strain that increases risk for interpersonal violence [49-52]. Researchers describe the need for prevention programs that emphasize connections between illicit substance use and exposure to SV, as well as reducing stigma and offering supportive environments to disclose these experiences [52]. Furthermore, despite the shared risk factors and the concurrence of SV and IPV [53]*,* none of these programs integrate strategies for addressing these co-occurring forms of violence. An integrated approach to violence prevention is particularly relevant to women in SUD treatment, whose histories are characterized by multiple incidents and types of interpersonal violence [54,55].

### Theoretical Framework

The Healthy Relationships and Interpersonal Violence Education (THRIVE) program is informed by the information, motivation, behavioral skills model, which posits that three constructs influence behavior change and its consequent effects on health outcomes: (1) information and knowledge about the behavior, (2) motivation to perform the behavior, and (3) the behavioral skills necessary to perform the behavior [56]. Regarding information and knowledge, the literature on interpersonal violence indicates that inaccurate knowledge regarding how to define or label sexual assault, intentions to engage in risky behavior, overestimations of peer engagement in risky sexual behavior, acceptance of gender role stereotypes, and endorsement of rape and partner violence myths are positively associated with SV exposure risk [57-62]. Motivational factors associated with protective behaviors and exposure to SV include supportive peer norms, intentions to engage in protective behaviors, and risk recognition related to SV and IPV [63,64]. Behavioral skills and behaviors that reduce the likelihood of exposure to SV include risk recognition, coping and resistance skills for risky situations, self-efficacy to perform these skills, protective behavioral strategies (eg, sexual assertiveness and safety planning), substance use harm reduction strategies, and help seeking [65-67]. THRIVE program components align with each of these theoretical and empirical risk and protective factors as depicted in Figure 1.

**Figure 1 figure1:**
[figure not shown]
Alignment of THRIVE Program Components with the IMB Model.

### Study Aims

The study will examine the feasibility and preliminary effectiveness of THRIVE, a PSS-delivered interpersonal violence prevention program for women in substance use treatment. The first objective is to determine program acceptability and feasibility. The second objective is to determine the preliminary effectiveness of THRIVE. Proximal outcomes include violence-related knowledge and attitudes, protective sexual and dating behaviors, and help seeking. Distal outcomes include exposure to SV, substance use, and mental health. These objectives will be achieved via a single-arm trial with at least 60 women in outpatient and residential substance use treatment.

## Methods

### THRIVE Program Development

We conducted preliminary program content development following an iterative process. We first developed content based on evidence-based and theoretically informed strategies from the literature (ie, the enhanced assess, acknowledge, act model and the information, motivation, behavioral skills model), as well as our prior prevention programs with college women [47,48,68]. Second, we adapted and refined the content based on 2 rounds of interviews with 2 expert consultants, 5 health care providers at substance use treatment clinics, 5 PSSs, and 5 women in SUD treatment. The interviews assessed feasibility and acceptability, the strengths and weaknesses of the program, preferred delivery modalities, and suggestions for improvement. Participants unanimously agreed that the content would be useful and appropriate for women in SUD treatment. Participants indicated that a flexible format would be preferred in terms of offering individual versus group sessions. The women in SUD treatment noted that they would respond well and prefer a PSS over a health care or mental health provider to deliver sensitive content related to sexual assault psychoeducation and substance use.

We added components specific to this population based on feedback from the participants. These include risk reduction information focused on drug use (in contrast to the primary focus on alcohol of most prevention programs), the addition of discussions on exchanging sex for drugs, a scenario-based skills-building component, increased engagement (question-and-answer and myths vs facts exercises), and handouts summarizing key takeaways.

### Intervention

The intervention consists of two 60-minute sessions delivered in-person by PSSs in either group or individual format. Groups consist of 5 to 10 individuals. The sessions include a combination of information; interactive exercises to fuel discussion on knowledge, attitudes, and behaviors; and skills-building activities. Handouts accompany each session with key takeaways and resources. Topics include (1) definitions of SV and IPV, (2) consent, (3) healthy versus unhealthy relationships, (4) help seeking and resources for trauma-related care, (5) protective behavioral strategies, (6) safe dating, (7) alcohol and drug safety (8) sexual assertiveness, (9) overcoming barriers to protective strategies, and (10) creating a behavior change plan. Table 1 presents the intervention content. In addition to the prevention education program, PSSs screen each participant for PTSD using the Primary Care PTSD Screen for DSM-5 (PC-PTSD-5) [69]. Participants who score ≥3 (indicating a potential PTSD diagnosis) are referred to local mental health providers who provide trauma-informed care. If participants are already enrolled in mental health care, the PSS ensure that the provider is informed of the participant’s PTSD symptoms.

**Table 1 table1:** The Healthy Relationships and Interpersonal Violence Education program content.

Sessions and topics			Content		Outcome measures		Information, motivation, behavioral skills model components

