##### Demographics

A demographics questionnaire assessed gender identity, race and ethnicity, and age. A participant log recorded recruitment site and intervention format.

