#### Statistical Analyses

To test the effects of THRIVE on primary and secondary outcomes, linear mixed effects model for continuous outcomes and generalized linear mixed effects models for binary outcomes will be used, with subject-specific random intercepts to account for the correlations of longitudinal outcomes measured after the intervention (week 2) and at 1-month and 3-month follow-ups. Covariates, such as recruitment sites, any demographic variables correlated with primary outcomes, type of substance use, and intervention format, will be included as fixed effects in all analysis models. The primary knowledge, attitude, and behavior outcomes will be continuous outcomes, and secondary outcomes such as experience of SV or IPV will be binary outcomes. In addition, with this model, we will also identify postbaseline time points where changes in outcomes from baseline are significant.

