## Results

Recruitment, enrollment, and data collection from the 3 sites was completed between June 2024 and March 2025. Of the 92 women recruited and enrolled, 71 (77%) completed the intervention and postintervention assessments, 58 (63%) completed the 1-month follow-up assessments, and 44 (48%) completed the 3-month follow-up assessments. Ten completers, 2 noncompleters, and 2 PSS completed exit interviews. Of the 92 enrolled participants, 45 (50%) were from the Prisma Health Addiction Medicine Center, 42 (47%) from Phoenix Center, and 3 (3%) from Magdalene Clinic. Of the 92 participants, 1 (1%) was American Indian or Alaska Native, 4 (4%) were Black, 1 (1%) were Hispanic, 79 (86%) were White, 2 (2%) identified as multiracial, and 3 (3%) identified as “other.” Racial and ethnic distribution is representative of the patient populations at the recruitment sites. The participants’ mean age was 35 (SD 9.87) years. The most commonly reported substances used included tobacco (79/92, 86%), cannabis (58/92, 63%), alcohol (55/92, 61%), amphetamine-type stimulants (58/92, 63%), and opioids (50/92, 54%; Table 3).

**Table 3 table3:** Types of substances used by enrolled participants (N=92).

Substance types	Participants, n (%)
Tobacco	79 (86)
Alcohol	55 (61)
Cannabis	58 (63)
Opioids (heroin, fentanyl, etc)	50 (54)
Amphetamine-type stimulants	58 (63)
Inhalants	19 (24)
Sedatives	47 (51)
Hallucinogens	32 (35)
Cocaine	44 (48)

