### Conclusions

Upon successful completion of this study, we expect to demonstrate the feasibility, acceptability, and preliminary effectiveness of THRIVE. This program will address gaps in the evidence base by emphasizing the critical intersection of violence and substance use, expanding effective strategies to a population considered high risk, and implementing a novel peer-delivered format to overcome barriers to care. The limitations of this approach include the use of a single-arm trial, underrepresentation of minoritized populations at our recruitment sites, and flexibility in program format that introduces some variability and could limit generalizability. If preliminary feasibility and efficacy are established, we will use the study findings to design future trials that minimize these limitations by using randomized controlled designs, oversampling underrepresented groups, and standardizing the delivery format. Our long-term goal is to develop an accessible, scalable, and efficacious prevention program that reduces the incidence of exposure to SV and IPV, substance use, and violence-related mental health disorders for women in substance use treatment. Ultimately, reducing exposure to SV and IPV is expected to reduce substance use escalation as well as sustain recovery from SUDs over the long term.

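### The model ignores correlation of change among women treated in the same group, so standard errors for change are understated if that correlation is positive

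*Protocol article*

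**What the plan says.** Under Intervention, the protocol article describes two 60-minute sessions "delivered in-person by PSSs in either group or individual format". It adds: "Groups consist of 5 to 10 individuals".

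Under Statistical Analyses, continuous outcomes get a linear mixed model and binary outcomes a generalized linear mixed model, "with subject-specific random intercepts to account for the correlations of longitudinal outcomes" after the intervention and at 1 and 3 months. Recruitment site, demographic variables, "type of substance use, and intervention format, will be included as fixed effects in all analysis models". The same section sets out the inference: "we will also identify postbaseline time points where changes in outcomes from baseline are significant".

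On the delivery data, the Demographics section says: "A participant log recorded recruitment site and intervention format". The Feasibility and Acceptability section adds that study logs held enrollment and attendance. Neither names a group identifier. The Conclusions list as a limitation the "flexibility in program format that introduces some variability and could limit generalizability"; dependence between women is not mentioned.

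**The concern.** Women in one group share a session, a date and a discussion. The Intervention section says the exercises are meant to prompt discussion of knowledge, attitudes and behaviors, which are the proximal outcomes. The Assessment Plan places the baseline and postintervention surveys immediately before and after the sessions, so group members also share the measurement occasion. Their changes may therefore be correlated.

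No stated model term captures this. A woman's random intercept links only her own repeated measures. A fixed effect for format shifts the mean for group against individual delivery, and one for site shifts the mean by clinic. Neither makes two women from the same group more alike than two women from different groups at the same site.

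Stable differences between groups cancel from a change score. Group effects that arise during or after the sessions do not, and they go straight into the standard error of change. The time-point tests would then reject too often, and any confidence interval built on the same standard error would be too narrow.

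**Working it through.** The article states no alpha, power, effect size, SD or ICC, and does not derive its target of 60 completers. There is no figure of its own to reproduce.

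**Inputs from the article**
- Group size m: 5 to 10 (Intervention). I use 7 as a middle value.
- Women with postintervention data: "71 (77%) completed the intervention and postintervention assessments" of 92 enrolled (Results).

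**Assumptions, because the article gives neither**
- s, the share of women treated in groups: 0.25, 0.5 or 1.
- ICC of change within a group: 0.01, 0.05 or 0.10.
- Equal group sizes, equal variance of change per woman, a continuous outcome, and a two-sided 5% test.

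**Formulas**
- Variance inflation of the overall mean change: V = 1 + s(m − 1)ICC.
- True SE divided by reported SE: √V.
- Shortfall of the reported SE: 1 − 1/√V.
- Actual type I error: 2[1 − Φ(1.96/√V)].

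Example with s = 0.5, m = 7, ICC = 0.05: V = 1 + 0.5 × 6 × 0.05 = 1.15; √V = 1.072; 1.96/1.072 = 1.828; type I error 6.8%.

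**Results at m = 7**

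| s | ICC | V | True/reported SE | Reported SE too small by | Type I error |
|---|---|---|---|---|---|
| 0.25 | 0.01 | 1.015 | 1.007 | 0.7% | 5.2% |
| 0.25 | 0.05 | 1.075 | 1.037 | 3.6% | 5.9% |
| 0.25 | 0.10 | 1.15 | 1.072 | 6.7% | 6.8% |
| 0.5 | 0.01 | 1.03 | 1.015 | 1.5% | 5.3% |
| 0.5 | 0.05 | 1.15 | 1.072 | 6.7% | 6.8% |
| 0.5 | 0.10 | 1.30 | 1.140 | 12.3% | 8.6% |
| 1 | 0.01 | 1.06 | 1.030 | 2.9% | 5.7% |
| 1 | 0.05 | 1.30 | 1.140 | 12.3% | 8.6% |
| 1 | 0.10 | 1.60 | 1.265 | 20.9% | 12.1% |

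Over the stated range of m (5 to 10) at ICC 0.10, the type I error is 7.4% to 10.4% with half the women grouped and 9.8% to 15.5% with all grouped. At s = 0.5, m = 7 and ICC 0.10, the 71 women carry the information of 71/1.30 = 54.6 independent women.

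**Simulation of the stated model.** The set-up was 71 women at four time points, with attrition to 58 and 44, a random intercept per woman, time as a factor, groups of 7 and 200 runs per setting. Format was a fixed effect in the half-grouped runs and was dropped when nearly all women were grouped.

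| Share in groups | ICC | True/reported SE | Type I error |
|---|---|---|---|
| Half | 0 | 0.92 | 5.0% |
| Half | 0.05 | 1.07 | 8.5% |
| Half | 0.10 | 1.20 | 7.5% |
| Nearly all | 0 | 0.95 | 4.0% |
| Nearly all | 0.05 | 1.11 | 6.5% |
| Nearly all | 0.10 | 1.28 | 13.0% |

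Monte Carlo error on the type I error is about 1.5 to 3 points. The runs therefore support the direction and rough size of the formula, not its decimals.

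**Number of groups.** At the smallest group size, 71/5 gives at most about 14 groups among completers, and about 7 if half were grouped.

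**The case against.** The strongest reply is that little depends on this. The study is a single-arm pilot with feasibility as its first objective. The Study Design section concedes that the design does not permit rigorous efficacy testing, and no alpha or significance-based decision rule is given. That limits the consequence. It does not correct the standard errors behind tests that the plan says it will run.

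A second reply is that a condensed article may leave extra random effects to a SAP. This has some force, but the article does state which random effects carry the correlation and which terms are fixed. The point is about that stated choice.

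A third is that the shared facilitator is weak evidence of group-specific correlation, since two peer support specialists served the whole study. That stands; the case rests on shared sessions, discussion and occasion.

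A reader might also infer more than the article supports:
- **That the inflation at s = 1 applies to this trial.** Delivery is mixed and the grouped share is not reported, so those rows are an upper case for their ICC and group size.
- **That the next trial's sample size will rest on these intervals or needs a group ICC.** The article says only that findings will inform future trials and that the delivery format will be standardized. If that format is individual, no group ICC is needed.
- **That a group identifier is ready to merge.** The logs are said to hold site, format and attendance. Nor does the article say whether a woman attended both sessions with the same group.

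**Conclusion.** The point holds in conditional form. The stated model omits within-group correlation of change, and any positive value makes the standard errors for change too small and the time-point tests anti-conservative. This is a matter of precision: mean change is not biased by it, and recruitment, retention, adherence and acceptability results are untouched.

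The size cannot be fixed from the article. On the assumed values it runs from negligible (5.2% against a nominal 5% with a quarter grouped and ICC 0.01) to material (12.1% with all grouped and ICC 0.10, where the true SE is 26% larger than reported). The conclusion assumes that some groups were run. The article implies this by logging format, adjusting for it and listing format flexibility as a limitation, but it reports no counts by format.

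**What to change.** 1. Build a session-group identifier from the attendance and session records, if it can be recovered. The Quality Assurance and Implementation section says a team member attended and rated each session, which may help. Give each individually treated woman her own cluster, and set a rule for women who changed group between sessions.
2. Fit a partially nested model: keep the random intercept per woman and add a group random effect that acts at the post-baseline waves, for group-treated women only. A group intercept constant over time would not do, because it cancels from change.
3. If that variance cannot be estimated reliably, use cluster-robust standard errors by group with a small-sample correction.
4. Report the number of women and groups by format, and the group ICC of change with its interval, as description. The ICC is useful for planning only if the next trial uses group delivery.
5. If group membership cannot be recovered, say so and present the time-point tests with the sensitivity range above.

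The cost is some record work, one identifier and one model term. Intervals will widen somewhat, and with at most about 14 groups the ICC will be imprecise.
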